#### Treatment

All included patients will receive a standard of care approach which involves either RC with extended pelvic lymph node dissection (ePLND) or TMT consisting of a visible complete TURb and radiochemotherapy. Radiochemotherapy consists of moderately hypofractionated radiotherapy to a dose of 55 Gy in 20 fractions to the bladder, in combination with a radiosensitizer. In case of clinically node-positive disease, the pelvic nodal areas are included in the radiotherapy field. Decision of local therapy is at the discretion of the patient unless there is a contraindication for one treatment option. If the patient is eligible, neo-adjuvant chemotherapy will be administered.

^18^F-FDG-PET-CT information concerning the pelvic lymph nodes will be used to guide local treatment i.e. adapting the ePLND template or radiotherapy field, if feasible.

According to the risk-group allocation, treatment will be intensified by adding MDT or immunotherapy, in treatment arm 2 or 3, respectively. Patients will not be randomized. Both surgery and stereotactic body radiation therapy (SBRT) can be applied as MDT for oligometastases. The SBRT procedure is described in detail in an additional file (see Additional file 3). In treatment arm 3, systemic immunotherapy will be initiated in case of ^18^F-FDG-PET-CT detected polymetastatic disease. The systemic immunotherapy protocol can be adjusted following changes in guidelines and/or reimbursement criteria.

In case of diagnosis of metastases on the conventional imaging before local treatment is started, the patient is excluded from the trial and metastatic bladder cancer standard of care is initiated.

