### Objectives

The primary endpoint is the 2-year overall survival (OS) rate defined as the percentage of patients alive at 2 years after diagnosis of MIBC. OS is calculated from time of diagnosis until death due to MIBC or other causes.

Secondary endpoints are progression-free survival (PFS, defined as time of diagnosis until progression: i.e. local (T2-T4 in case of of TMT)/locoregional recurrence or extra-pelvic metastases), distant metastasis-free survival (DMFS, defined as time of diagnosis until occurrence of distant metastasis on repeated imaging), disease-specific survival (DSS, defined as time of diagnosis until death due to MIBC) and quality of life (QOL) evaluated by the general EORTC QOL questionnaire QLQ-C30 (version 3) and the bladder cancer specific module QLQ-BLM30. The added diagnostic value of ^18^F-FDG-PET-CT compared to conventional imaging will be evaluated. If neo-adjuvant chemotherapy is administered, the treatment response will be evaluated on the repeated ^18^F-FDG-PET-CT. A biopsy specimen of the bladder, obtained after transurethral resection of the bladder (TURb) as well as urine and blood samples will be collected for validation of predictive biomarkers by evaluating the correlation between response to therapy and outcome (PFS, DMFS, DSS and OS) with in literature reported biomarkers determined on biopsy specimen of the bladder, obtained after TURb.

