### Inclusion criteria

Histopathology-proven MIBC on TURb or ≥ T3 on conventional imaging treated with MIBC radical treatmentT1–4 N0–3 M0 MIBC on conventional imaging (thoracic CT and abdominopelvic CT/ MRI)Age > 18 yearsWHO 0–2Willingness to undergo ^18^F-FDG-PET-CTWillingness to undergo MDT or immunotherapy, in case of diagnosis of oligometastatic or polymetastatic disease on ^18^F-FDG-PET-CT, respectivelyWillingness and ability to provide a signed informed consent according to ICH/GCP and national/local regulations

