### Intervention

#### Imaging

Conventional imaging, consisting of standard thoracic CT and abdominopelvic CT (or MRI), will be performed prior to the radical local therapy. In case of neo-adjuvant chemotherapy, conventional imaging will be performed prior to and after neo-adjuvant chemotherapy. After the second cycle of chemotherapy, MRI bladder will be performed to evaluate provisional therapy response. In addition to and at timing of the conventional imaging patients will receive an ^18^F-FDG-PET-CT. We aim to perform the ^18^F-FDG-PET-CT within 1 month of the thoracic CT and abdominopelvic CT (or MRI).

The ^18^F-FDG-PET-CT procedure is described in detail in an additional file (see Additional file 2).

Conventional imaging images will be evaluated by experienced radiologists in uro-oncology. ^18^F-FDG-PET-CT images will be reviewed and analyzed by a nuclear medicine physician and a radiologist experienced in reading PET-CT images. Evaluation of the ^18^F-FDG-PET-CT images will occur blinded to the conventional imaging or vice versa in case the ^18^F-FDG-PET-CT is performed first.

After ruling out presence of distant metastases on conventional imaging and evaluation of the ^18^F-FDG-PET-CT’s, patients will be allocated to the appropriate treatment arm:
Arm 1: ^18^F-FDG-PET-CT ➜ T1–4 N0–3 M0Arm 2: ^18^F-FDG-PET-CT ➜ T1–4 N0–3 M1 (≤3 metastases)Arm 3: ^18^F-FDG-PET-CT ➜ T1–4 N0–3 M1 (> 3 metastases)

If no neo-adjuvant chemotherapy is administered, group allocation is based on the findings of the single ^18^F-FDG-PET-CT. In case of neo-adjuvant chemotherapy, group allocation is based on ^18^F-FDG-PET-CT with the highest number of distant metastases. Thus, patients who show a decrease of the total number of metastases or a complete response on the second ^18^F-FDG-PET-CT, will be allocated based on the result of their first ^18^F-FDG-PET-CT.

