### Statistical analyse

#### Sample size

This is a multicentric prospective phase II study in which 156 patients will be enrolled. A confidence interval for the 2-year OS was estimated using the Kaplan Meier survival estimates and corresponding confidence intervals (type ‘log-log’). These Kaplan Meier survival estimates are based on binomial proportions. When the true proportion of survival is 63% for arm 2 + 3, a sample size of 35 patients (39 when taking into account 10% drop-out rate) in group 2 + 3 yields 80% power to show that the proportions of patients surviving at 2 years, is 38% or more using an exact binomial test at alpha level 5% [12]. We expect 1/4 patients to have a positive ^18^F-FDG-PET-CT, based on the unpublished observations of [name] et al.

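### Patients whose restaging scan after neo-adjuvant chemotherapy shows metastases are excluded after enrolment, which can raise the 2-year OS of arms 2+3 and deletes PFS and DMFS events

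*Protocol article*

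**What the plan says.** Under Inclusion criteria, patients must be "M0 MIBC on conventional imaging (thoracic CT and abdominopelvic CT/ MRI"), and the Exclusion criteria repeat this. Under Imaging, "In case of neo-adjuvant chemotherapy, conventional imaging will be performed prior to and after neo-adjuvant chemotherapy", each time with a PET-CT. Allocation to arms takes place "After ruling out presence of distant metastases on conventional imaging and evaluation of the" PET-CTs. With chemotherapy it follows whichever PET-CT shows more distant metastases, and a patient whose metastases shrink in number or disappear is still allocated on the first scan.

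Under Treatment: "In case of diagnosis of metastases on the conventional imaging before local treatment is started, the patient is excluded from the trial". Such patients move to standard care for metastatic disease. The sentence is not limited to baseline imaging.

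Under Objectives, the primary endpoint is "defined as the percentage of patients alive at 2 years after diagnosis of MIBC", and "OS is calculated from time of diagnosis until death due to MIBC or other causes". PFS (with extra-pelvic metastases as one event) and DMFS (distant metastasis on repeated imaging) also start at diagnosis. Under Sample size, arms 2+3 are tested against a fixed 38%, with no randomized control.

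**The concern.** For a patient on neo-adjuvant chemotherapy, the exclusion can act well after enrolment, and its trigger is an outcome: visible progression before local treatment. The handling is also asymmetric. A PET-positive patient who responds completely to chemotherapy is kept in arm 2 or 3, while one whose restaging CT or MRI turns positive is removed.

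Three things are at stake. The 2-year OS of arms 2+3 may look better than that of the PET-positive patients who were enrolled, with no benefit from metastasis-directed therapy or immunotherapy. With a single-group test against a fixed figure, no control group carries the same selection to cancel it. Next, the excluding event is itself a PFS and DMFS event as the protocol defines them, so the rule deletes those events. Finally, restaging PET/CT pairs in which conventional imaging did detect disease would drop out of the diagnostic comparison.

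**Working it through.** **Step 1: the plan's own figure.** Inputs from Sample size: 2-year OS of 63% under the alternative and 38% under the null, exact binomial test, alpha 5% (sidedness not stated), 35 patients, 10% drop-out, one quarter PET-positive.

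- Two-sided 5% (upper tail 2.5%), n = 35: success needs at least 20 alive. P(X ≥ 20 | 35, 0.38) = 0.0167 and P(X ≥ 20 | 35, 0.63) = 0.815. Power is 79.7% at n = 33 and 75.5% at n = 34, so 35 is the first size to reach 80%.
- One-sided 5%, n = 35: success needs at least 19 alive, with exact alpha 0.0367 and power 0.892.
- 35 / 0.9 = 38.9, rounded up to 39, and 39 / 0.25 = 156.

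The stated 35, 39, 156 and 80% reproduce on the two-sided reading. The sample size is not in error.

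**Step 2: effect of the exclusion.** Let f be the share of enrolled PET-positive patients removed at restaging and q their 2-year OS. The document gives neither, so both are assumptions. Assume also that 38% is the true 2-year OS of all enrolled PET-positive patients, meaning no treatment benefit. The patients who remain then have

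p = (0.38 − f·q) / (1 − f),

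and the chance of false success is P(X ≥ 20 | 35, p). For example, f = 10% and q = 10% give (0.38 − 0.01) / 0.90 = 0.411.

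| f | q = 0%: OS, false success | q = 10%: OS, false success | q = 20%: OS, false success |
|---|---|---|---|
| 2% | 38.8%, 2.1% | 38.6%, 2.0% | 38.4%, 1.9% |
| 5% | 40.0%, 3.0% | 39.5%, 2.6% | 38.9%, 2.2% |
| 10% | 42.2%, 5.4% | 41.1%, 4.1% | 40.0%, 3.0% |
| 15% | 44.7%, 9.5% | 42.9%, 6.4% | 41.2%, 4.1% |
| 20% | 47.5%, 16.5% | 45.0%, 10.2% | 42.5%, 5.8% |

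The planned exact value is 1.7% and the nominal upper tail 2.5%. On the one-sided reading (at least 19 of 35, planned 3.7%), the corner f = 20%, q = 0% gives 26.3%.

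**Step 3: one concrete case.** Suppose 39 PET-positive patients are enrolled, 4 are excluded at restaging and die within 2 years, and 20 of the rest are alive at 2 years. Without the excluded, 20/35 = 57.1% meets the criterion of 20. With them, 20/39 = 51.3% does not, because 39 patients require 22 alive (two-sided) or 21 (one-sided).

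**The case against.** **The benchmark.** The 38% carries a citation, but the article does not describe the population behind it. If that population was also free of metastases on conventional imaging up to treatment, the selection would match and the bias would shrink. A reader might infer that an upward bias against 38% is established. It is not: the text establishes a selection relative to all enrolled PET-positive patients, and the rest depends on a population that cannot be seen.

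**The tested group.** Allocation follows restaging, so an excluded patient was never formally in arm 2 or 3, and the trial asks about metastases seen on PET but not on conventional imaging. This stands as a description of the design. It does not remove the problem, because the survival clock starts at diagnosis while membership depends on what happens afterwards.

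**The reach of the rule.** A reader might take it to affect every patient, or to remove from the diagnostic comparison those whose PET came first and whose baseline CT then showed M1. The entry criteria already exclude the latter. For patients without chemotherapy the rule largely repeats eligibility. The point is confined to restaging.

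**An analysis plan that is not shown.** Being excluded from the trial need not mean being excluded from the analysis, and Follow up and data collection provides 3-monthly survival status after progression. The text does not say whether this covers patients excluded under Treatment. If survival is not collected after exclusion, no later plan can restore them, so the protocol is the place to settle it.

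**The size.** At f of 5% or less the shift is at most 2 percentage points, and the false-success chance (3.0% or less) stays close to the nominal 2.5%. This stands.

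**Conclusion.** The point holds for patients given neo-adjuvant chemotherapy. The protocol removes enrolled patients for progression inside the survival interval, keeps complete responders, and deletes events that it defines for PFS and DMFS. The direction is upward if the excluded survive worse than those retained, which is plausible for overt metastatic progression but not documented.

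The size cannot be derived from the document. For 2% to 20% excluded with 2-year OS of 0% to 10%, and with 38% applying to all enrolled PET-positive patients, OS without benefit is about 38.6% to 47.5% and false success about 2% to 16.5%, against 1.7% planned. The lower end is negligible and the upper end would undermine a positive result. The figures show what the rule could do and do not estimate what it will do.

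**What to change.** Replace exclusion from the trial with leaving the study treatment pathway, with care as the protocol already states. Then:

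- Continue survival follow-up for these patients on the 3-monthly schedule in Follow up and data collection.
- Include every enrolled patient who was M0 on the conventional imaging used for eligibility in the primary 2-year OS analysis.
- Group them by the allocation rule under Imaging: the PET-CT with the most metastases, including the restaging PET-CT if done, otherwise the first. Without this, a patient negative on the first PET who progresses at restaging has no defined group.
- Count metastases at restaging as PFS and DMFS events, and keep restaging PET/CT pairs in the diagnostic comparison.
- Report the analysis without these patients as a sensitivity analysis.

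This keeps the test at its planned exact level when the benchmark refers to all enrolled PET-positive patients. The costs are an amendment, survival contacts for probably a few patients, and a possibly slightly lower reported OS. The tested group will include some patients treated with metastatic standard care, so the primary result describes the whole PET-guided strategy from enrolment, and the sensitivity analysis describes those who reached allocation. An alternative is to define the population and time origin at allocation after restaging, but that needs a benchmark selected in the same way, which the document does not describe.

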### Follow up and data collection

An overview of the different follow-up moments and associated assessments and investigations is presented in Fig. 2. Adverse events (AE) will be assessed using the Common Terminology Criteria for Adverse Events version (CTCAE) 5.0 [14].. Patients will be instructed by the investigator to report the occurrence of any AE. The investigator assesses and records all AE observed during the AE reporting period from inclusion until 5 years after inclusion. QOL will be assessed using the European Organisation for Research and Treatment of Cancer (EORTC) QLQ-C30 [15] and QLQ-BLM30 [16] questionnaires. Imaging studies are done conform standard of care. In case of TMT a routine cystoscopy is advocated every 3 months during the first year of follow-up and 6-monthly thereafter until 5 years. Patients will be followed up until death or disease progression defined as per: Response Evaluation Criteria in Solid Tumors (RECIST)-criteria [17]. Once disease progression has been confirmed, survival status will be assessed 3-monthly until death, withdrawal of consent or the end of the study, whichever occurs first. Patients who are no longer followed in the center of inclusion or who refuse follow-up visits but are willing to have telephone follow-up will be contacted by phone at the scheduled follow-up time points.

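### Disease follow-up ends at first progression with only survival status named afterwards, so the plan states no collection of the distant metastases that DMFS must count after a locoregional first progression

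*Protocol article*

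**What the plan says.** Four statements in the protocol article bear on this point.

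- **When follow-up ends** (Follow up and data collection): "Patients will be followed up until death or disease progression defined as per: Response Evaluation Criteria in Solid Tumors (RECIST)-criteria".
- **What is collected afterwards** (same section): "Once disease progression has been confirmed, survival status will be assessed 3-monthly until death, withdrawal of consent or the end of the study". No metastasis status or imaging result is named for this period. The section says only that imaging follows standard of care.
- **What counts as progression for PFS** (Objectives): "progression: i.e. local (T2-T4 in case of of TMT)/locoregional recurrence or extra-pelvic metastases".
- **What DMFS measures** (Objectives): "DMFS, defined as time of diagnosis until occurrence of distant metastasis on repeated imaging". Nothing limits this to metastasis as the first event.

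Subsequent analyses plans 2-year Kaplan-Meier estimates of DMFS for each treatment group, and log-rank comparisons between groups.

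Two neighbouring statements matter for the limits of the point. Disease-specific survival is given as "DSS, defined as time of diagnosis until death due to MIBC". For adverse events, the investigator "records all AE observed during the AE reporting period from inclusion until 5 years after inclusion".

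**The concern.** PFS needs only the first progression, so stopping disease assessment there does it no harm. DMFS needs the first distant metastasis, which may come after a pelvic or bladder recurrence. A patient whose first progression is locoregional leaves disease follow-up with the DMFS event still possible, and the only item then named is whether the patient is alive.

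The stop is stated outright, so this is more than detail that a condensed article leaves out. An analysis plan can choose between censoring these patients and keeping them at risk, but it cannot restore metastasis dates that were not collected. Either choice can flatter DMFS. Censoring is informative if locoregional recurrence raises the risk of distant spread. Keeping patients at risk counts later unseen metastases as non-events.

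DMFS is a secondary endpoint, but a relevant one in a trial whose purpose is to adapt treatment to distant disease.

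**Working it through.** **1. The plan's own figure.** The article gives no figure for DMFS. Its only design figure concerns overall survival in arms 2 + 3: 38% against 63% alive at 2 years, exact binomial test. Taking the 5% level as two-sided (2.5% in the upper tail), 35 patients with success at 20 or more alive gives alpha 0.0167 and power 0.815. Then 35 / 0.9 = 38.9, rounded up to 39, and 39 / 0.25 = 156. The stated 35, 39 and 156 reproduce. None of them depends on DMFS, and survival status is still collected after progression.

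**2. The rules side by side, for a patient whose first progression is locoregional.**

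| Endpoint | Event needed after that progression | Named in the text? |
|---|---|---|
| PFS | none, the event has occurred | not needed |
| OS | death | yes, 3-monthly survival status |
| DMFS | first distant metastasis on imaging | no |

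**3. Size of the effect on DMFS.** All rates are assumptions, because the documents give none. The model uses constant hazards over t = 2 years and ignores death.

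- D = 2-year risk of distant metastasis without prior local recurrence, so d = -ln(1 - D) / 2.
- L = 2-year risk of locoregional recurrence, so l = -ln(1 - L) / 2.
- After locoregional recurrence the distant hazard is h = k·d.
- True freedom from distant metastasis = exp(-(l+d)t) + l·[exp(-ht) - exp(-(l+d)t)] / (l + d - h).
- Estimate if censored at recurrence = exp(-dt) = 1 - D.
- Estimate if kept at risk as metastasis-free = exp(-(l+d)t) + [l / (l+d)]·[1 - exp(-(l+d)t)].

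*Worked example:* D = 30%, L = 20%, k = 3.

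- d = 0.1783, l = 0.1116, l + d = 0.2899, h = 0.5350.
- exp(-2 × 0.2899) = 0.7 × 0.8 = 0.560, and exp(-2h) = 0.7³ = 0.343.
- True = 0.560 + 0.1116 × (0.343 - 0.560) / (0.2899 - 0.5350) = 0.560 + 0.099 = 65.9%.
- Censored = 70.0%, an overstatement of 4.1 points.
- Kept as metastasis-free = 0.560 + (0.1116 / 0.2899) × 0.440 = 72.9%, an overstatement of about 7 points.

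With k = 2 instead, the true value is 67.7% and the same two estimates are 2.3 and 5.2 points too high.

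*Range:* D from 20% to 40% and L from 10% to 30%. Overstatement of 2-year DMFS in percentage points:

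| Distant hazard after recurrence | Censored at recurrence | Kept as metastasis-free |
|---|---|---|
| unchanged (k = 1) | 0 | 1.0 to 5.8 |
| twice (k = 2) | 0.8 to 4.1 | 1.8 to 10.0 |
| four times (k = 4) | 2.2 to 9.2 | 3.2 to 15.0 |

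For k of 1 or more the error is never downward. It is zero only with censoring and k = 1.

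**The case against.** The strongest reply is that the text does not prove any loss of data. Standard-of-care imaging may go on after progression, patients are still contacted every 3 months, and the assessment schedule is in a figure that is not shown. A reader might infer that later metastases are never recorded. The documents do not support that. They support only that no such collection is stated and that the stated rule ends disease follow-up.

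Second, the stop rule uses RECIST progression, while the recurrence wording belongs to the PFS definition. Some bladder recurrences found at cystoscopy after trimodality therapy may not trigger the stop. This narrows the affected group and leaves its boundary unclear. Locoregional progression seen on imaging remains affected.

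Third, every rate behind the size is assumed, and the handling of these patients in DMFS may properly be left to an analysis plan. Both points stand, so the bias has to be stated conditionally.

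Three further inferences are tempting and should not be made.

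- **That disease-specific survival is also too favourable.** Deaths are tracked after progression, and cause of death is an ordinary case report form item that an article may omit. If cause were missing, the error could go either way, depending on how those deaths were coded.
- **That late toxicity is lost in patients who progress.** The adverse event period runs to 5 years with no stated stop at progression. The two sentences sit awkwardly together, but that is an ambiguity and does not show a loss.
- **That a comparison of cystectomy with trimodality therapy is distorted.** No such contrast is named among the planned analyses.

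**Conclusion.** The point holds for DMFS. The follow-up rule does not support the DMFS definition in patients whose first progression is locoregional. If the rule is followed as written, 2-year Kaplan-Meier DMFS is too favourable when these patients are censored and recurrence raises the distant hazard, or when they are carried as metastasis-free. With censoring and a hazard 2 to 4 times higher, the overstatement is roughly 1 to 9 points. This rests on assumed constant hazards, on the assumed risks above and on ignoring death. The direction is firmer than the size, and it too is conditional.

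The primary endpoint and the sample size are untouched. For disease-specific survival and adverse events, only a confirmation and a reconciliation of wording are called for. The point is worth correcting, because uncollected dates cannot be restored at analysis, but it does not threaten the trial's main conclusion.

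**What to change.** - In Follow up and data collection, let locoregional progression end follow-up for PFS only. At the 3-monthly contacts already planned, record the date and site of first distant metastasis from standard-of-care imaging, until distant metastasis, death or end of study.
- Say whether the RECIST rule or the recurrence wording under Objectives decides when a patient leaves disease follow-up.
- Confirm that cause of death is recorded for deaths after progression.
- Reconcile the 5-year adverse event period with the end of follow-up at progression, so that sites know which sentence applies to a patient who has progressed.

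The cost is a few case report form fields and some extra data entry after progression. No visits, scans or treatment changes are added. The article describes the study as still ongoing, so at that time the change could still be made.
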